### Outcome measures

Feasibility of a full-scale randomised controlled trial is the essential outcome of the feasibility trial. Feasibility for this would be confirmed if the feasibility trial demonstrates (1) a conservative recruitment rate of 10% of all eligible patients, i.e. screening 10 or fewer patients to gain a single recruit, (2) recruitment of 65% of target participants, i.e. recruiting 20 of the target number of 30, (3) retention of 80% of participants with an equivalent proportion of outcome data collected, and (4) continued patient and clinician compliance to the manualised tinnitus counselling.

Outcomes for the feasibility trial include completeness of a set of validated questionnaires. These reflect typical components of an RCT test battery in tinnitus and are considered most likely to capture the anticipated therapeutic benefits of the intervention:Tinnitus Functional Index (TFI) [23] to measure the severity and impact of tinnitusTinnitus Cognitions Questionnaire (TCQ) [24] to assess positive and negative cognitions associated with tinnitusClinical Outcomes in Routine Evaluation - Outcome Measure (CORE-OM) [25] to assess general well-beingHealth Utilities Index (HUI) 15Q [26] to assess health-related quality of life and cost-utilityWorking Alliance Inventory (WAI) [27] to measure the quality of the therapeutic alliance (patient and clinician versions)Section 4 of the Client Service Receipt Inventory (CSRI) [28] to measure the use of health and social care

The participant will complete the baseline study questionnaires in advance of their first audiology appointment and again immediately at the end of treatment (excluding the CSRI which is only completed at follow-up). To determine a candidate primary outcome measure of long-term impact, the questionnaires (including the CSRI) will be administered again via post at 6-month follow-up. One telephone or email reminder to complete the follow-up questionnaires will be used if the questionnaires have not been returned within 2 weeks.

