##### Inclusion criteria

For inclusion in the feasibility trial, patients must reflect the typical population that might be expected to take part in a phase 2 clinical trial. The typical population includes adults aged 18 and over, comprises more males than females, shows a trend towards increasing age to a peak of between 60 and 69 years [21] and a bias towards people of higher deprivation/level of education [22]. The sample is also likely to contain a proportion of people who suffer from comorbid mental health conditions, e.g. anxiety and depression, and medical conditions, e.g. hypertension and diabetes mellitus [21]. The majority are also likely to have some degree of hearing loss [22]. Participants will be required to demonstrate the intellectual/cognitive capacity to provide informed consent and have sufficient mobility to attend clinics. No exclusions will be made on the basis of previous experience with psychological services. All patients will be enrolled at or before their first visit to audiology and have a primary complaint of tinnitus. Patients will also be required to present with a clinically relevant need, determined by a questionnaire score of >24 on the Tinnitus Functional Index (TFI) [23] indicating that tinnitus is at least a moderate problem. Offering this intervention to patients without such a clinically relevant need may be considered unnecessary treatment. All participants must be willing to complete questionnaires and to take part in follow-up semi-structured interviews about their experiences of taking part in the study.

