### Randomisation

Participants will be 1:1 randomised using the randomisation function in Microsoft Excel. First participants will be assigned a number between 1 and 10 for each of the three sites, according to chronological order of recruitment. For each site, these numbers will be given another random number using the Excel randomisation function and the participants 1 to 10 for each site will be ordered according to their associated randomly generated number. Those with the greatest five random numbers per site will be allocated to TAU. This process will be completed by telephoning a member of the research unit not involved in the trial after the participant has been screened as eligible and provided informed consent.

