### Statistical analysis

The feasibility trial will not include any hypothesis testing since its primary purpose is to determine whether a full-scale trial can be conducted. Descriptive statistics will be used to confirm (1) the number of eligible participants at each site (participating sites will routinely administer the TFI questionnaire to all patients presenting with a primary complaint of tinnitus), (2) willingness of patients to take part in a trial and be randomised (number of eligible participants willing to participate), (3) number of eligible participants recruited per month, (4) number of participants retained at discharge and follow-up, and (5) percentage completion rate of questionnaire outcome measures, including questions unsuccessfully and incorrectly completed.

Descriptive statistics, including standardised mean averages, standard deviation (SD), standard error and confidence intervals, will also be used to compare the evaluative and discriminative properties of the tinnitus specific outcome measures. This will provide data on a potentially best single measure to use, should this work proceed to an explanatory RCT. Responsiveness to change of the tinnitus questionnaires used will be compared by assessing change to standardised mean scores across assessment time points within patient groups that reported an improvement, worsening or no change in their tinnitus-related health.

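### Feasibility criterion 1 sets one threshold on two denominators, eligible patients and screened patients, which agree only if every screened patient is eligible

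*Protocol article*

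**What the plan says.** Under Outcome measures, the protocol article lists four conditions under which the feasibility of a full-scale trial would be confirmed. The first is "a conservative recruitment rate of 10% of all eligible patients, i.e. screening 10 or fewer patients to gain a single recruit". The second is a minimum number of recruits, given as "recruiting 20 of the target number of 30".

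Three other sections bear on what screened and eligible mean:

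- **Inclusion criteria and Exclusion criteria.** Eligibility requires a TFI score above 24, and also capacity to consent, mobility and willingness to complete questionnaires and interviews. Exclusions cover medically treatable tinnitus, inability to communicate in English and participation in other tinnitus management research.
- **Randomisation.** Allocation takes place "after the participant has been screened as eligible and provided informed consent".
- **Statistical analysis.** To establish the number eligible at each site, "participating sites will routinely administer the TFI questionnaire to all patients presenting with a primary complaint of tinnitus". Willingness to take part is measured as the "number of eligible participants willing to participate", and recruitment per month is also counted among eligible participants. No total of screened patients is listed.

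**The concern.** The two halves of criterion 1 are joined as if one restated the other. The first has eligible patients as its denominator and the second has screened patients. By the article's own account, screening decides who is eligible, and the TFI cut-off is there to set aside patients without a clinically relevant need. The plan therefore allows for some screened patients not being eligible, and in that case the two halves are different thresholds.

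The trial will test no hypotheses, so the four feasibility conditions are its decision rule. A threshold that can be read in two ways leaves room for the reading to be settled after the counts are known.

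**Working it through.** **Inputs.** The eligible form is "a conservative recruitment rate of 10% of all eligible patients", taken here as recruits/eligible of at least 0.10. The screened form is "screening 10 or fewer patients to gain a single recruit". Both come from Outcome measures, as do the minimum of 20 recruits and the target of 30. The share p of screened patients who are eligible is not given; the range 0.4 to 1.0 is assumed.

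**Step 1: the plan's own figure.** 1/0.10 = 10. A rate of 10% is one recruit per 10 patients, so the figure reproduces when both forms use the same patients as denominator.

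**Step 2: separate denominators.** Let S be screened, E = pS eligible and R recruited.

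- Eligible form: R/E ≥ 0.10, so E ≤ 10R, and hence S/R ≤ 10/p.
- Screened form: S/R ≤ 10, which is the same as R/E ≥ 0.10/p.

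| Assumed p | Screened per recruit at 10% of eligible (10/p) | Share of eligible at 10 screened per recruit (10%/p) | Largest S passing the eligible form at R = 20 (200/p) |
|---|---|---|---|
| 1.0 | 10.0 | 10.0% | 200 |
| 0.9 | 11.1 | 11.1% | 222.2 |
| 0.8 | 12.5 | 12.5% | 250 |
| 0.7 | 14.3 | 14.3% | 285.7 |
| 0.6 | 16.7 | 16.7% | 333.3 |
| 0.5 | 20.0 | 20.0% | 400 |
| 0.4 | 25.0 | 25.0% | 500 |

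The screened form at 20 recruits allows at most 200 screened, whatever p is.

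**Step 3: direction of the conflict.** Since E ≤ S, R/E ≥ R/S. Any data with S/R ≤ 10 therefore have R/E ≥ 0.10, and passing the screened form guarantees passing the eligible form. The converse fails when 10 < S/R ≤ 10/p.

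**Step 4: illustrations, both with p = 0.6 assumed.**

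- At the minimum of 20 recruits: 250 screened and 150 eligible. 20/150 = 13.3% passes; 250/20 = 12.5 screened per recruit fails.
- At the target of 30 recruits: 400 screened and 240 eligible. 30/240 = 12.5% passes; 400/30 = 13.3 screened per recruit fails.

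These counts were chosen to show the conflict and do not forecast this trial's data.

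**The case against.** The best defence is that the article has one working denominator and the gloss only explains 10% as one in ten. The main clause names eligible patients, the related counts under Statistical analysis are of eligible patients, and no screened total is listed. On the listed counts only the eligible form can be computed. This stands as a good reason to keep the eligible form. It does not make the second half of the sentence harmless, because that half still states a different threshold within the rule.

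A second defence is that screening might mean working through patients already known to be eligible from the routine TFI. The two forms would then agree. That reading is possible, and the participant flow chart, which was not available for this review, may bear on it. The text does not state it, however, and the Randomisation section treats eligibility as something that screening establishes.

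A third defence is that this is a 30-patient feasibility study, criterion 1 is one of four conditions, and neither the randomisation nor any effect estimate depends on it. That is fair and limits the severity.

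A reader might also infer that a full trial's screening workload would be forecast wrongly. The article does not support this. Under Participants it ties the timeframe of a full trial to the predicted recruitment rate of two participants per month per site, not to screened patients per recruit.

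**Conclusion.** Criterion 1 is internally inconsistent and should be fixed. The two forms agree only at p = 1. For any smaller p, the eligible form tolerates 10/p screened per recruit against 10 for the screened form, for example 12.5 at p = 0.8 and 20 at p = 0.5. That the thresholds differ whenever p is below 1 follows from the text, provided screened has its ordinary meaning of assessed for eligibility. The size of the gap rests entirely on an assumed p.

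Two stronger conclusions might be drawn, and neither holds. One is that the arithmetic is wrong; it is not, since only the denominator changes. The other is that the feasibility decision is generally open to either answer. Disagreement is confined to the band above 10 and up to 10/p screened per recruit, always with the eligible form passing and the screened form failing. The article gives no figures from which to judge whether this trial will fall in that band.

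**What to change.** State criterion 1 once, with one denominator: *at least 10% of patients who meet the eligibility criteria are recruited*. Delete the gloss about screening 10 or fewer patients. This matches the counts already listed under Statistical analysis and costs one sentence.

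If screened per recruit is also of interest, define screened, add that count to the Statistical analysis list, where it does not now appear, and report it as a descriptive figure outside the feasibility rule. The cost is one extra count in the screening log. Breakdowns by site and confidence intervals would be optional reporting detail and are not needed to mend the criterion.

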### Interventions

Psychologically informed treatment plus TAU: the intended purpose of the manual is to provide audiologists with a resource to support their work with people who have tinnitus in a psychologically informed therapeutic alliance to identify individual needs, set joint goals, reach shared and informed decisions and promote patient self-management. It is designed to go beyond the directive education and advice that might be considered TAU. Based on estimates from current practice, patients will participate in approximately five sessions, each lasting 1 h on average, delivered by an audiologist who attended a two-day training workshop on the manual.

The manual is divided into nine sections (Table 1). Section 1 provides the background and overview of the manual, including the processes and skills for developing a relationship with the patient. Section 2 involves assessment through a standardised interview, where the aim is for individual patient needs to be identified and a therapeutic alliance to begin. The rationale for psychologically informed treatment will then be discussed (section 3) prior to collaborative goal setting and treatment planning (section 4). Based on individual need, the audiologist and patient will work on relevant areas of tinnitus education (section 5) and management/self-management strategies (section 6). These include managing the emotional consequences of tinnitus, rapid relaxation, managing fear and avoidance behaviours, changing unhelpful thoughts and beliefs, promoting physical exercise, promoting good sleeping habits, attention, monitoring and acceptance, and sound therapy (enrichment). The treatment concludes with a focus on relapse prevention (section 7). Section 8 is a bibliography containing references related to the intervention and further reading for the audiologist or patient. The appendices (section 9) contain materials used for training in the manual. Audiologists will be guided on appropriate treatment areas to cover and resources to use from an accompanying ‘toolkit’ (Table 2). They will receive periodic peer supervision and from the manual trainers.

**Table 1 Tab1:** Psychologically informed treatment for tinnitus manual contents

1. Introduction	
1.1.Background	
1.2.Overview of manual	
2. Patient assessment	
3. Rationale for psychologically informed treatment	
4. Goal setting/treatment planning	
5. Patient education	
6. Patient management/self-management	

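### The schedule exempts only the CSRI from the baseline pack, so the patient Working Alliance Inventory falls due before there is an alliance to rate

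*Protocol article*

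**What the plan says.** The Outcome measures section of the protocol article lists six instruments: TFI, TCQ, CORE-OM, HUI, WAI and section 4 of the CSRI. The WAI is there "to measure the quality of the therapeutic alliance (patient and clinician versions").

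The timing follows in the same section. "The participant will complete the baseline study questionnaires in advance of their first audiology appointment". The protocol then sets a repeat of this set at discharge, with a single exception: "again immediately at the end of treatment (excluding the CSRI which is only completed at follow-up"). For the last time point, "the questionnaires (including the CSRI) will be administered again via post at 6-month follow-up". The Abstract (Methods/design) gives the same three time points for the quantitative measures and makes no exception.

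The Interventions section describes the manual's assessment interview as the point at which "the aim is for individual patient needs to be identified and a therapeutic alliance to begin". Under Inclusion criteria, "All patients will be enrolled at or before their first visit to audiology".

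Completeness of the questionnaires is a named outcome of the feasibility trial. Progression criterion 3 asks for "retention of 80% of participants with an equivalent proportion of outcome data collected". In Statistical analysis, item 5 reports the percentage completion rate and includes questions that were not completed or were completed wrongly.

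**The concern.** The WAI asks about the working relationship between a patient and the clinician treating them. A participant who fills in the pack before the first audiology appointment has not yet worked with that clinician. The form can be left blank or answered about nobody in particular, and neither response is information.

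In many trials this would be a small nuisance. Here completion of the battery is one of the things being measured, to judge whether the battery suits a larger trial. Blank baseline WAI forms would be failures created by the schedule, but they could be read as poor acceptability of the questionnaire set. Forms filled in anyway would count as complete while carrying invalid answers. If baseline forms also enter criterion 3, the same artefact reaches a progression rule.

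**Working it through.** **Step 1: is the WAI due at baseline?** The scheduling sentence names one exception, the CSRI. That exception is needed only if the sentence otherwise covers the full list. The WAI is on the list and is not excepted, so the patient WAI is due at baseline, end of treatment and 6 months.

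**Step 2: does an alliance exist then?** The baseline pack precedes the first appointment. In the manual arm the alliance is said to start at the assessment interview, which comes later. The usual-care arm has no equivalent statement, but enrolment is at or before the first audiology visit in both arms, so the same reasoning applies.

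**Step 3: count the patient forms** (from Outcome measures).
- Baseline: TFI, TCQ, CORE-OM, HUI, WAI = 5
- End of treatment: the same 5
- Follow-up: the same 5 plus CSRI = 6
- Total: 5 + 5 + 6 = 16, of which 5 + 6 = 11 are after baseline

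**Step 4: effect on pooled completeness.** The protocol's 80% is a threshold with no derivation, so there is no planned figure to reproduce. The following are assumptions and are not in the protocol: each form has equal weight, every baseline WAI is blank, all other baseline forms are complete, and a share *r* of later forms is returned.

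- WAI kept at baseline and blank: (4 + 11*r*) / 16
- WAI removed from baseline: (4 + 11*r*) / 15

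| *r* | Kept, blank | Removed | Loss (points) |
|---|---|---|---|
| 1.00 | 15/16 = 93.75% | 15/15 = 100% | 6.25 |
| 0.90 | 13.9/16 = 86.9% | 13.9/15 = 92.7% | 5.8 |
| 0.80 | 12.8/16 = 80.0% | 12.8/15 = 85.3% | 5.3 |
| 0.75 | 12.25/16 = 76.6% | 12.25/15 = 81.7% | 5.1 |

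**Step 5: when could this change a decision?** Setting each expression equal to 0.80:
- Kept: *r* = (0.80 × 16 − 4) / 11 = 8.8/11 = 80.0%
- Removed: *r* = (0.80 × 15 − 4) / 11 = 8/11 = 72.7%

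The data half of criterion 3 changes from pass to fail only when later return is at least 72.7% but below 80.0%. The criterion also requires 80% retention. Within that window the schedule alters the overall result only if retention holds at 80% while the return of later forms falls short of it.

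**Step 6: the zero cases.** If criterion 3 counts only post-baseline data, the baseline WAI is in neither numerator nor denominator and the loss is 0. If participants fill the form in and the answers are accepted, the numerical loss is also 0, but the completion rate then includes invalid answers.

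**The case against.** The strongest reply is that the article never names the WAI at baseline. Its phrase for the baseline set could mean a subset specified in the full protocol, which is not shown, and the flow chart is missing from the text reviewed. This limits certainty but does not remove the point. The article chose to give instrument-level timing and excepted only the CSRI. If the baseline set were a subset without the WAI, the end-of-treatment repeat of that same set would omit the WAI too, so the sentence would still need correcting.

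A second reply is that criterion 3 is tied to retention, which Statistical analysis counts at discharge and follow-up, so baseline forms may not enter it. That stands as a plausible reading. The text does not settle it, and this is why the effect on criterion 3 is conditional.

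A third is that the trial's own record of unsuccessful or incorrect answers would reveal an unanswerable form. It might, but only after the data had been collected.

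Some stronger inferences are tempting, and the protocol does not support them:
- *The clinician WAI is also due at baseline.* The scheduling sentence concerns what the participant completes. It gives no baseline time point for the clinician version, so that version is left out of the count above.
- *WAI change from baseline is spoiled.* No such analysis is planned. The responsiveness comparisons are confined to the tinnitus-specific questionnaires, and there is no hypothesis testing.
- *Completeness is capped at 4/5 = 80%, exactly the threshold.* That is the baseline visit alone, which no criterion tests. The pooled ceiling is 15/16 = 93.75%, so the WAI by itself cannot fail the criterion.

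**Conclusion.** The scheduling error stands on the current wording: the patient WAI is placed where it has no valid referent. The certain consequence is for the questionnaire completion rate, which would be lowered by blanks or contaminated by invalid answers. The consequence for criterion 3 depends on a counting rule that the article does not give. It is about 5 to 6 points over later return rates of 75% to 100%, under equal weighting and with all baseline WAI forms blank, and zero if only post-baseline data count. It could tip a borderline result and no more. This is a modest correction that does not threaten the trial's conclusions, but it is worth making because completeness is one of the trial's own outcomes.

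**What to change.** In Outcome measures, name the WAI beside the CSRI as not completed at baseline, and keep it at end of treatment and at 6-month follow-up. In Statistical analysis (item 5) and in criterion 3, state that baseline WAI is not in the completion denominator. One sentence saying whether other baseline forms count in criterion 3 would remove the remaining ambiguity.

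A WAI after an early treatment session would be an optional addition; the correction does not need it.

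The cost is a change to the schedule wording and to the questionnaire packs. Participants have one form fewer at baseline, and no other outcome or time point changes.

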### Qualitative interviews and focus groups

Clinicians delivering the manualised treatment and patients receiving it will be invited to partake in semi-structured interviews of approximately 1 h to discuss their experiences of the intervention and for treatment fidelity to be explored. Patient interviews will be carried out 4 weeks following their last appointment to capture continued compliance with treatment techniques whilst not compromising recall. Clinician interviews will be conducted after discharge of their final patient. The interviews will be audio-recorded and conducted by authors, [name] and [name], transcribed and analysed using a thematic analysis approach [29]. Initial analysis of the qualitative data will be conducted by [name] and the study team, including members of the NIHR Nottingham Biomedical Research Centre Patient and Public Involvement (PPI) panel. Emerging themes will be discussed in two focus groups with (i) audiologists and (ii) patients, to ensure that the themes and any identified barriers and facilitators to treatment implementation and maintenance of self-management are accurately representative of patient and audiologist experience. The purpose of this outcome is to identify which components of the manualised care worked well, why and which elements were not useful. It is important to establish what was successful and unsuccessful since the intervention development started with patient and clinician opinion of what is important rather than based on which components of treatment are better than others.

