The specific aims are:To develop a treatment manual for a trained audiologist to use when providing psychological support for people with tinnitusTo conduct a feasibility trial to establish whether this manualised tinnitus treatment including core counselling elements versus treatment as usual (TAU) can be evaluated at the level of a large scale RCTTo conduct qualitative interviews with participating patients and audiologists to gather perspectives on the feasibility and acceptability of the manualised intervention

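### Interview invitations follow receipt of the manual, not allocation to it, so patients who never attend are left out and early stoppers have no set point of approach

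*Protocol article*

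**What the plan says.** The section *Qualitative interviews and focus groups* of the protocol article sets both the frame and the timing. The frame is: "Clinicians delivering the manualised treatment and patients receiving it will be invited to partake in semi-structured interviews". The timing, with its reason, is: "Patient interviews will be carried out 4 weeks following their last appointment to capture continued compliance with treatment techniques"; the sentence adds that recall should not suffer. On purpose, the same section says: "The purpose of this outcome is to identify which components of the manualised care worked well, why and which elements were not useful".

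The third aim, at the end of *Background*, is to use interviews with patients and audiologists to "gather perspectives on the feasibility and acceptability of the manualised intervention". The Abstract gives the interviews the same role.

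*Inclusion criteria* makes interview willingness a condition of entry for both arms: "All participants must be willing to complete questionnaires and to take part in follow-up semi-structured interviews". It describes these interviews as covering experience of being in the study, which is wider than experience of the manual's components.

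The article does not say whether, when or how patients who never start the manual, or who stop early, will be approached.

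**The concern.** Receipt and attendance both happen after randomisation, and both may depend on how acceptable a patient finds the offer. A frame tied to them can lose the people with least enthusiasm for the manual. The interviews are meant to show what was not useful as well as what was, and *Discussion* says the trial will inform changes to the manual and the design of the next trial. Reasons for not starting or for stopping bear directly on both.

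No other listed source clearly supplies those reasons at first hand. None of the questionnaires in *Outcome measures* is described as measuring acceptability; the Working Alliance Inventory measures the therapeutic relationship. *Statistical analysis* counts who is retained but lists no reasons for loss. Clinicians can describe patients who stopped, but only second-hand, and they may never have met a non-starter.

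**Working it through.** The plan gives no figure for the interview sample, so there is none to reproduce. The check sets the rule against each type of patient in the manual arm, then asks whether the plan's numbers can size the gap.

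**Step 1. Can non-starters arise?** Yes. *Inclusion criteria* allows enrolment before the first audiology visit, and *Randomisation* places allocation after screening and consent. A patient can therefore be allocated to the manual and then not attend.

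**Step 2. The rule applied to three types of patient.**

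| Patient allocated to the manual | Receiving it? | Has a last appointment? | Position under the rule |
|---|---|---|---|
| Attends to planned discharge | Yes | Yes, known at the time | Invited, timing clear |
| Starts, then stops attending | In part | Yes, the last one attended, but recognised as last only afterwards | Not excluded; point of approach not set |
| Attends no session | No | No | Outside the frame |

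The stated reason for the timing, continued use of the techniques, fits the first row best. The text does not limit patient interviews to those who completed or were discharged, so the second row cannot be read as an exclusion.

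**Step 3. Size of the manual arm.** *Randomisation* says: "Those with the greatest five random numbers per site will be allocated to TAU". With 10 patients per site and 3 sites, 5 × 3 = 15 go to usual treatment and 30 − 15 = 15 to the manual.

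**Step 4. Does the retention criterion size the gap?** Criterion (3) in *Outcome measures* is "retention of 80% of participants", with a matching share of outcome data. At full recruitment it tolerates 30 × (1 − 0.80) = 6 losses: 3 in the manual arm if split equally, and anything from 0 to 6 otherwise. These are not counts of patients missed by the interviews, for two reasons:

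- Retention is counted at discharge and at follow-up, and the 6-month questionnaires are postal. A patient who finishes treatment, is interviewed at 4 weeks and then does not return the 6-month forms is lost to retention but was interviewed.
- In the other direction, a patient who never attends could still return postal questionnaires, and so supply follow-up data without being in the interview frame.

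**Step 5. What can be stated.** If k of the 15 are non-starters or early stoppers who are not approached, 15 − k can be interviewed. Taking k from 0 to 3 as an assumption leaves 15 down to 12. The documents give no non-attendance rate, so k cannot be fixed more closely.

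**The case against.** The strongest case on the other side has four parts.

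- *Drop-outs are not excluded.* Someone who attends some sessions has received part of the manual and has a last appointment, and an interview held later than 4 weeks would be a timing deviation, not a bar. This stands. A reader might infer that only completers are interviewed and that acceptability is therefore judged only by those who stayed. The text does not support that. Retention and compliance are also separate feasibility criteria, and the treating clinicians are interviewed.
- *The bias cannot be quantified.* A reader might take the tolerated 20% loss, say that 3 of 15 are missed, and contrast 12/12 = 100% acceptability among stayers with 12/15 = 80% in the arm. Neither figure follows. Retention loss is not interview loss, as Step 4 shows. The interviews are analysed thematically, with no acceptability proportion or threshold. The contrast also assumes that every leaver disliked the manual and every stayer liked it. This objection stands in full.
- *Non-starters cannot comment on components they never met.* This is true of the components. They can still say why the offer was not taken up, which bears on acceptability and falls within the wider interview topic given in *Inclusion criteria*.
- *A condensed article may leave interview sampling to the full protocol.* This is fair for detail on how withdrawn patients are contacted. But the article does state who is invited and when, and the point concerns that stated rule.

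**Conclusion.** The point holds in a limited form. Defining the interview frame by receipt leaves out patients randomised to the manual who never attend. Early stoppers remain eligible, but the rule sets no point at which to approach them. The views of the first group, and possibly of the second, may therefore be missing from the main evidence on acceptability, and retention counts will not supply their reasons.

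The number affected is an assumption: a few of 15 manual-arm patients, possibly none. No numerical bias can be claimed. This is a cheap improvement to a stated rule, not a flaw that undermines the trial. It rests on the article's wording alone; the full protocol may already cover early stoppers.

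**What to change.** In *Qualitative interviews and focus groups*:

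1. Define the patient frame as everyone randomised to the manual arm. The entry condition on interview willingness already covers them.
2. Time the interview at 4 weeks after the last attended appointment or, for non-starters and those who stop early, once non-attendance is confirmed. State what counts as confirmed.
3. Ask non-starters and early stoppers why they did not start or why they stopped.
4. State in the report how many interviewees were non-completers.

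The cost is a few extra interviews and the effort of contacting people who have disengaged. Some will decline, so the gap may narrow without closing.
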